## Study Description

### 1. Study Purpose and Rationale

1.1 Purpose: The proposed study is a randomized controlled trial (RCT) that will rigorously evaluate the effectiveness and cost-effectiveness of delivering a multimedia evidence-based intervention (E-WORTH which is an acronym for Empowering African-American Women on the Road to Health) and streamlined HIV testing to prevent HIV and other sexually transmitted infections (STIs) with Black/African-American (hereafter referred to as Black) women drug users in probation, parole or alternative to incarceration programs (ATI hereafter) sites in New York City (NYC), compared to streamlined HIV testing alone. Repeated assessments will occur at baseline and 3, 6, and 12-months post intervention. The primary outcome will be to reduce cumulative incidence of biologically confirmed STIs (i.e., Chlamydia, gonorrhea and trichomonas. This study has the following specific aims:

### 1.2. Primary Aims

1. To test the comparative effectiveness of E-WORTH versus Streamlined HIV Testing on primary outcomes of decreasing biologically confirmed STIs and the number and proportion of unprotected sexual acts at the 12-month follow-up and secondary outcomes of reducing drug use, increasing utilization of drug treatment, linkage to HIV care and ART adherence (for HIV+ participants), decreasing partner violence and recidivism.
2. To test if the effectiveness of E-WORTH on study outcomes is moderated by client characteristics (e.g. client subgroups defined by socio-demographics and psychosocial characteristics)
3. To estimate the costs and comparative cost-effectiveness of E-WORTH versus Streamlined HIV Testing on STI infection rates, drug use and projected number of HIV cases averted at the 12-month follow-up.

4. To examine qualitatively and quantitatively how multi-level theory-driven factors may influence the fidelity of implementation and effectiveness of E-WORTH and Streamlined HIV testing on study outcomes.

1.3 Rationale: Despite extremely high rates of HIV and STIs that have been found among women on probation, parole or ATI programs nationwide, to date, WORTH is the only intervention that has been found to be efficacious in increasing condom use and reducing sexual risks among justice involved women in the U.S. Our recent study of 337 drug-involved women on probation or community supervision in NYC found that 17% of the 221 Black women tested positive for HIV and 30% tested positive for an STI . The HIV rate found among Black women on probation indicates a highly concentrated epidemic, comparable to rates in sub-Saharan Africa; however, no HIV prevention or testing services are provided in NYC probation sites. The proposed study will address this critical gap in services for Black women drug users in probation settings by testing the effectiveness and cost-effectiveness of the 5-session multimedia E-WORTH intervention.

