At each interim time point as well as after study completion, analyses will follow the data analysis plans for primary aims described in the original proposal. Interim analyses will focus on the study's primary aims. If at any of the interim analyses the statistical significance for all biological outcomes related to primary aims (i.e., cumulative STI incidence), exceeds the a priori  $\alpha < .05$  criterion at that time point, the study will be stopped since the inference will be that significant benefit of assignment to one study arm over the other will have already been demonstrated. We note that this represents two-sided hypothesis testing since demonstrating benefit with respect to disease prevention of one intervention over the other (regardless of the content of that intervention) is of public health value and importance. With respect to futility, stopping rules are concerned with effect size estimates indicating a null result is inevitable given the planned total sample size. Stopping a study in such circumstances avoids additional expenditure of time, fiscal, and human resources that would nevertheless ultimately result in lack of evidence of superiority of one intervention over the other. At each interim analysis time point, a post hoc power analyses will be conducted to determine the minimum sample size needed to achieve 80% power to reject the null hypothesis given point estimates and standard errors of efficacy estimates using data collected to date. If the estimated minimum sample size for power analyses using  $\alpha =$

.05 exceeds the planned enrollment of N=420 women for all of the biological and self-reported behavioral outcomes associated with the primary aims, the investigative team will notify the NIDA Program Official (PO) of such findings. Based on the magnitude of the difference between the estimated minimum sample sizes needed for 80% power and targeted sample size, in addition to recruitment rates to date, the investigative time and NIDA PO will discuss and agree whether the study should be stopped due to reasons of futility or whether modifications to the study design/protocols (e.g., increasing planned enrollment, hiring of additional recruitment staff, etc.) can be implemented to avoid futility.

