## **Data Analyses Plan:**

The analytic approach is built upon the investigative team's prior HIV prevention randomized clinical trials, including an intention-to-treat approach, handling missing data using both complete case and multiple imputation approaches, attrition analyses to investigate non-ignorable nonresponse, and sensitivity analyses to ascertain robustness of findings against violation of model assumptions (e.g., distribution requirements, heteroscedasticity, independence). Mixed-Effects Generalized Linear Models will be used to account for the non-independence in measures due to repeated measures with the same person. These models build upon  $g(E[(Y_{ij}|\mathbf{x}_{ij}]]) = \mathbf{x}'_{ij}\boldsymbol{\beta}$  where  $Y_{ij}$  is the outcome variable of interest for the  $i$ th participant at the  $j$ th timepoint. The components of  $\boldsymbol{\beta}$  will be intervention assignment, baseline attributes for the outcome variable, and selected sociodemographic variables based on the unbalanced randomization or relevant literature. The  $g(a)$  function represents a link function that can properly model the outcome variable as a function of measurement unit or distribution. Hypothesis testing follows the form "Assignment to E-WORTH will be associated with significantly lower/higher on outcome variable  $Y$  at the 12-month follow-up or over the follow-up period compared to assignment to the control condition where 'lower' or 'higher' is chosen in the direction of reduced risk. To test the difference in the new incidence of any STI (primary outcome) at the 12-month follow up, logistic regression models will be used. To test the effects for behavioral outcomes over the entire follow-up period, mixed-effects Poisson or negative binomial regression will be used for the number of condomless acts of sex (primary outcome), mixed-effects linear regression will be used for proportion of protected acts of intercourse, and mixed-effects logistic regression models will be used for binary behavioral outcomes.

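### The current text names one, two or three primary outcomes with no order or alpha split; if each is tested at .05, familywise error is about 9–10% for two and 10–14% for three

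*Supplement*

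**What the plan says.** Three current sections give three different lists.

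- **One outcome.** Protocol section 1.1: "The primary outcome will be to reduce cumulative incidence of biologically confirmed STIs". Section 2.1 also uses the singular, for the STI assay. Section 3.2 uses the plural but describes only the assay.
- **Three outcomes.** Protocol section 1.2, Aim 1: "primary outcomes of decreasing biologically confirmed STIs and the number and proportion of unprotected sexual acts at the 12-month follow-up".
- **Two outcomes.** Data Analyses Plan: "To test the difference in the new incidence of any STI (primary outcome) at the 12-month follow up, logistic regression models will be used", and then a count model for the "number of condomless acts of sex (primary outcome" label. It goes on, "mixed-effects linear regression will be used for proportion of protected acts of intercourse", without calling that outcome primary.

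Sections 1.1 and 1.2 read the same in both copies of the protocol in the supplement, so this is not a change between versions.

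On error control, section 13 (Interim Analyses and Stopping Rules) sets .05 for cumulative STI incidence in the efficacy stopping rule and adds: "We note that this represents two-sided hypothesis testing". The futility paragraph of that section applies .05 to a sample-size re-estimation for all biological and behavioral outcomes of the primary aims. Section 13's one remark on Type I inflation concerns the number of interim looks, not the number of outcomes. Section 2.2 and the Data Analyses Plan state one hypothesis per outcome, with no sequence, alpha split or rule for success.

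The time points differ as well. Aim 1 puts the behavioral outcomes at 12 months; the Data Analyses Plan tests them over the whole follow-up.

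**The concern.** A reader of the final report could not tell from the plan whether a null STI result with a significant fall in self-reported condomless acts meets the primary objective. Under section 1.1 it does not. Under Aim 1 or the Data Analyses Plan a primary outcome has been met. The sample size in section 2.3 rests on STI incidence as the limiting outcome, and section 3.5 uses the assay to give a more objective measure than self-report. Leaving the order open therefore matters most in the case where the two kinds of outcome disagree.

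Several primary outcomes, each tested at .05 with nothing linking them, also raise the chance that at least one is falsely significant. This problem is separate from the interim looks and would remain if the interim rule were mended.

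**Working it through.** **1. The plan's own figure.** The documents state no familywise error rate. The nearest figure is the STI sample size in section 2.3: control incidence 20.5%, 50% reduction, 80% power, effective N 372, then 378, then 420.

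Poisson regression with a binary predictor split 1:1, base rate .205, β = ln(.5) = −.693, two-sided .05:

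N = (1.960·√4 + 0.842·√6)² / (.205 × .480) = (3.920 + 2.062)² / .0985 ≈ 363, within 3% of 372.

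Two-proportion formulas for .205 against .1025 give 379 (arcsine), 381 (unpooled) and 388 (pooled). The attrition step is exact: 378 / .90 = 420. So 372 is consistent with spending the whole two-sided .05 on STI. It is not proof of that, because a one-sided Wald Poisson formula gives 377.

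**2. Independent tests, each at two-sided .05.**

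- One outcome (section 1.1): 5%.
- Two outcomes (Data Analyses Plan): 1 − .95² = 9.75%.
- Three outcomes (Aim 1): 1 − .95³ = 14.3%.

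**3. Correlated tests.** The documents give no correlations, so these are assumptions. The figures come from 1.5 million draws of multivariate normal test statistics.

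Two outcomes, STI and number of acts:

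| Correlation | 0 | .3 | .5 | .7 | .8 |
|---|---|---|---|---|---|
| At least one false result | 9.75% | 9.5% | 9.1% | 8.4% | 7.8% |

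The 9–10% range therefore assumes a correlation between STI and condomless acts of no more than about .5.

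Three outcomes:

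| Number–proportion correlation | 0 | .5 | .8 | .9 | .999 |
|---|---|---|---|---|---|
| STI independent of behavior | 14.3% | 13.6% | 12.4% | 11.7% | 10.0% |
| STI–behavior correlation .3 | 13.8% | 13.2% | 12.1% | 11.4% | 9.7% |

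Number and proportion come from the same reported acts, so high correlations are plausible. As their correlation nears 1, three tests behave like two.

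**4. One direction only.** Counting only false results in favor of E-WORTH (.025 per test, independent): 1 − .975² = 4.9% for two and 1 − .975³ = 7.3% for three, against 2.5% for one.

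**5. What splitting alpha would cost.** Pooled two-proportion formula, 189 per arm, ignoring the small ICC inflation:

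| STI level | Power at N = 378 | N for 80% power |
|---|---|---|
| .05 | 79.1% | 388 |
| .05/2 | 70.1% | 470 |
| .05/3 | 64.5% | 516 |

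A fixed sequence avoids this loss. Each step is taken only after the one before is significant, so the first true null hypothesis reached is tested once at .05, and the familywise rate stays at 5% at the final analysis.

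**The case against.** The strongest reply is that STI already leads. Sections 1.1 and 2.1 name it alone, section 2.3 calls it the limiting outcome, and the efficacy stopping rule turns on it alone. The section that specifies the tests labels two outcomes primary, not three. Section 2.2 frames a separate hypothesis for each outcome, so a significant result supports a claim about that outcome only, and familywise error is the natural measure only if any single success counts as trial success. This has force. It rules out treating Aim 1's list as the governing one, and it is why the size has to be given for each list. It does not supply an order or a success rule, and it does not explain why the Data Analyses Plan gives the same label to STI and condomless acts.

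Two further points stand. No level is stated for the final behavioral tests; .05 is inferred from the futility paragraph. And section 2.2 sends the primary-outcome models to a Table 4, and section 13 refers to the original proposal. Neither is shown, so a rule there cannot be excluded, though it would not reconcile sections 1.1, 1.2 and the Data Analyses Plan.

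A reader might infer that the plan allows the trial to be declared positive on any one of three outcomes, with an error rate of 12–14%, or about 19% once the interim looks are added. The documents do not support that. They state no success rule at all. The 12–14% range belongs to Aim 1's list alone and needs a number–proportion correlation no higher than about .8. The 19% mixes in the interim rule, which is a separate problem.

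**Conclusion.** The inconsistency is real and should be fixed before analysis: one, two or three primary outcomes depending on the section, and no order, alpha split or success rule shown. If each is tested at two-sided .05, the chance of at least one false primary result in either direction, before interim looks, is about 9–10% under the Data Analyses Plan and about 10–14% under Aim 1. Under section 1.1 it stays at 5%. These figures rest on the inferred .05 for the behavioral tests, on assumed correlations, and on counting either direction, which fits the two-sided stance in section 13. They are familywise rates; the plan states no familywise level for them to breach. STI's lead role can be read from several sections, so this calls for a reconciliation of the text and not a redesign.

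**What to change.** - Use one primary list in protocol sections 1.1, 1.2 and 2.1 and in the Data Analyses Plan, and align section 3.2 with it.
- Test STI first at the full two-sided .05, with the interim rule mended separately. Test the number of condomless acts only if STI is significant.
- Treat the proportion of protected acts as secondary, as the Data Analyses Plan in effect does, or make it the last step of the sequence.
- State one time point for the behavioral outcomes: 12 months or the whole follow-up.
- If a step fails, report the later outcomes as estimates with confidence intervals only.

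The cost is wording. STI power and the sample size of 420 do not change. The real downside is the gate: with about 80% power for STI, 1 − .80 = 20%, so a confirmatory behavioral claim is blocked about one time in five even if the assumed STI effect is real. The team should accept that knowingly. Splitting alpha equally across two outcomes would keep the behavioral claim independent of STI, but by the pooled two-proportion formula it would cut STI power at 378 from 79.1% to 70.1%.

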## 2. Study Design and Statistical Procedures

2.1. Overview of Study Design: This RCT will be conducted with 420 drug-involved Black women recruited from probation, parole or designated ATI program sites in NYC. Women will be randomly assigned to either (1) the 5-session E-WORTH intervention condition that includes an individual Streamlined HIV Testing session or (2) a Streamlined HIV Testing session (See Section

C.9). Fortune providers will deliver both intervention conditions at the Fortune sites in Long Island City or Castle Garden in Manhattan. In extenuating circumstances (e.g. participants are located too far away from these sites), Fortune providers may also deliver both conditions at a NYC DOP sites approved by the appropriate DOP Assistant Commissioner or at our community research office. Women assigned to either condition will continue to receive all services provided by probation, parole or designated ATI program staff. Women who test positive for HIV in either condition will receive HIV post-test counseling and linkage to treatment using the CDC Counseling, Testing and Referral (CTR) Protocol. In month 14, recruitment of participants will begin. We will enroll an average of 14 women per month and complete enrollment by month 45. Self-reported data on behavioral outcomes will be collected from participants via audio computer-assisted self-interview (ACASI). The primary outcome will be measured via biological assay for infection by *Neisseria gonorrhea*, *Trichomonas*, and *Chlamydia trachomatis*, the most common STIs found among women in NYC.

Repeated measurements will take place at baseline and at 3, 6, and 12 months' post-intervention. For Aim 3, we will collect cost data from a variety of sources every six months from months 14-55. At midpoint during enrollment (Month 23), we will conduct a qualitative study on multi-level factors for Aim 4.

2.2 Statistical Procedures: The analytic approach is built upon the investigative team's prior HIV prevention RCTs, which involves an intention-to-treat approach, handling missing data using multiple imputation, and conducting sensitivity analyses to quantify robustness of findings based on models and their assumptions. Descriptive statistics will characterize the sample and measurement distributions to ensure proper application of multivariate methods. We will use multiple imputation to handle missing data. Attrition analyses will identify variables to be

included in MI models to handle nonignorable nonresponse. Preliminary analyses include bivariate analyses to identify unadjusted associations among variables. Variables significantly associated with outcome variables and attrition, as well as significantly different across study arms, will be included as covariates during hypothesis testing. Generalized Linear Mixed Models (GLMM) and Generalized Estimating Equations (GEE) will be used to account for the nonindependence in measures arising from: (1) “autocorrelation” due to repeated measures with the same person; and (2) “intraclass correlation [ICC]” arising from group membership. The data analytic approach for testing hypotheses with outcome specific models for primary outcomes is presented in Table 4. Analytic strategies for secondary outcomes will follow a similar approach.

Hypothesis testing will implement an intention-to-treat approach. We will employ Generalized Linear Mixed Models (GLMM) and Generalized Estimating Equations (GEE) to account for the non-independence in measures arising from: (1) "autocorrelation" due to repeated measures with the same person; and (2) "intraclass correlation [ICC]" arising from partners who are reporting on conjoint behaviors. Hypothesis testing for Aim 1 follows the form “Assignment to E-WORTH will be associated with significantly lower/higher outcome variable Y at the 12-month follow-up compared to assignment to Streamlined HIV Testing” where ‘lower’ or ‘higher’ is chosen in the direction of reduced risk. The selection of outcome models build upon  $g(Y_{ij|x_{ij}}) = x'_{ij}w$  where  $Y_{ij}$  is the outcome of interest for the  $i$ th participant at the  $j$ th time point. The multilevel nature of the data is accounted for by modeling each predictor variable’s coefficient in the vector as dependent on group membership: where the  $i$ th participant is a member of the  $g$ th group that determines the group characteristics (i.e., elements of the vector  $w$ ) used to estimate model fit parameters in vector. The components of  $w$  will be treatment assignment, baseline attribute for the outcome variable, and those variables selected during preliminary analyses noted earlier. The  $g()$  function represents a link function that can model the outcome as a function of measurement unit or distribution.

**2.3 Power Analyses:** From ICC estimates based on the previous WORTH trial, variance inflation factors were calculated to generate effective sample sizes used in G\*Power for Aim 1. For cumulative STI incidence, we assumed a 50% reduction (on a background cumulative incidence of 20.5%) to be clinically meaningful to detect via Poisson regression; for behavioral outcomes, projected means, standard deviations, allow for effect size  $f^2$  to be calculated and used in G\*Power. Results for primary outcomes (Figure 3) indicate that 80% power is achieved for the rate-limiting outcome (i.e., cumulative STI incidence) with an effective sample size of 372 participants; translating to a sample size of 378 participants after accounting for ICC. We then increased the starting sample size to 420 to safeguard against attrition (modeled as a complete loss of 10% of data as conservative estimate since the efficacy trial of WORTH achieved a 91% retention rate at 12-month follow-up and many of those cases provided data at earlier assessment points, thus were not “fully” missing). For secondary outcomes, power analyses participants/arm indicate 80% power to detect differences for effect sizes  $f^2 = .03$  to  $.04$  (for  $\alpha = .1$  TO  $.5$ ) with sample sizes as low as 369.

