### 3.2. Overview of Study Participation

This randomized controlled trial will be conducted with 420 drug-involved Black women from probation, parole or designated ATI program sites located throughout communities in NYC heavily affected by HIV and STIs. Eligible women will be randomly assigned to: (1) E-WORTH consisting of an individual evidence-based Streamlined HIV Testing session followed by a 4-session group-based multimedia HIV intervention (E-WORTH) or (2) an individual Streamlined HIV Testing session alone (Streamlined HIV Testing), which will serve as the comparison condition. Both conditions will be delivered at two Fortune Society Sites (located in Harlem and in Long Island City). If participants live too far to attend sessions at these sites, Fortune staff may also deliver intervention sessions at our community research site or at a NYC DOP site approved by the appropriate DOP Assistant Commissioner. Repeated assessments will occur at baseline and 3, 6, and 12-months post intervention. For participants residing out of New York City during their follow up period, or are otherwise prevented from traveling to study sites to complete a follow up assessment, we will send a link to follow up assessments directly to the participant's e-mail on a password protected PDF document. We will conduct repeated assessments and qualitative in-depth interviews on multi-level factors that may influence the effectiveness of E-WORTH and Streamlined HIV Testing on study outcomes with Fortune providers delivering the interventions, frontline probation, parole or designated ATI program staff (e.g. probation officers), probation administrators and probation clients. Self-reported data on behavioral outcomes will be collected from participants via audio computer-assisted self-interview (ACASI). Primary outcomes will be measured via biological assay for infection by *Neisseria gonorrhea*, *trichomonas*, and *Chlamydia trachomatis*, the most common STIs found among women in NYC.

We will also conduct qualitative interviews with 20 E-WORTH participants who reported episodes of homelessness and depression when completing assessments at baseline, 3-, 6- and/or 12-month. The goal of these interviews is to better understand the relationship between

homelessness and depression among women involved in the criminal justice system who are also at risk for HIV and other STIs.

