### 3.7. Compensation

All participants will be reimbursed up to \$340 for their time for completing the screening and the assessments. Below is the compensation that participants or potential participants in the randomized controlled trial study will receive for study activities. This includes incentives to cover travel expenses to office sites.

\$5 for eligibility screening interview

Two-fare metrocard currently valued at \$6

\$55 for enrollment (that is \$35 for completing the baseline assessment, vaginal swab specimen - also referred to as STI testing, and \$20 for orientation and HIV testing)

\$20 bio retesting

\$50 for getting Bio Results and Bio Treatment in the same day. Transportation and change of contact info is included.

Plus, an extra \$5 if the participant arrives on time for the enrollment meeting

\$100 (\$15.00 for each of the 4 intervention sessions you complete + an extra \$5 for being on-time to each session. You will also receive \$6 for transportation.)

\$50.00 for completing the 3-month follow-up interview

\$60.00 for completing the 6-month follow-up interview

\$65.00 for completing the 12-month follow-up interview and STI test and HIV test

\$50 CBO referral bonus (10 participants)

\$20 participant referral bonus (10 participants)

\$-15 childcare

\$5 change of contact information

\$35 Graduated participants will be invited to have a qualitative interview

They will also receive a light meal at each visit to the office.

In addition, participants and CBO staff are also eligible to earn the following if they refer others to the study:

\$5.00 for every person they refer to the study that is later screened. When a CBO staff successfully refers 10 eligible participants who enroll and attend session one, they will receive a bonus of \$50. When a participant makes 10 successful referrals, they will receive a bonus of \$20. The person referred must meet the basic criteria of the study. That is, she must be Black, 18 years or older and must be on probation or recently completed probation in the past 90 days.

\$10.00 for every person referred to the study who is later enrolled and completes their first follow up meeting.  
\$15 Childcare incentive will now be offered to women for assessments.

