\$50 incentive now will be offered to be able to encourage hard to reach participants who were also tested positive for an STI and need to be treated as soon as possible before they are due for 12 month follow up appointment. Hard to reach participant will be provided her STI results and escorted by a Research Assistant to the most convenient Free STI Clinic. Incentive is included delivering the STI Results, Getting Treated and Confirming the Treatment, Transportation and Changing Contact Information when its all done in the same day.

Lastly, participants are also eligible to receive an additional \$5.00 if they change their contact information (i.e. phone number, mailing address, etc...) and report the change to a member of the study.

For the mixed methods study with Fortune Society employees who are assigned to the E-WORTH Project will receive the following compensation for study activities. NYC Department of Probation does not allow their staff to receive any compensation for study activities.

\$30 for survey interviews (repeated every six months from the study start to month 56)  
\$30 for qualitative interview. (\$30 + \$5 for transportation= \$35)

For the in-depth interviews focusing on homelessness and depression, *participants will receive \$50 in a gift card and \$6.00 round trip metrocard to cover travel expenses.*

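### Visits dated from the end of the intervention give E-WORTH a longer interval to the 12-month STI swab than control, and the cumulative-incidence label does not match what appears to be a single follow-up swab

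*Supplement*

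**What the plan says.** **Visit timing.** Section 3.2 says: "Repeated assessments will occur at baseline and 3, 6, and 12-months post intervention". Section 2.1 uses the same anchor. Neither says which day ends the intervention for a woman who does not complete it.

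**Length of each arm.** Under section 3.5 (Randomization), both arms receive the HIV testing session immediately, and for control that is the whole intervention. E-WORTH women then have four group sessions. If fewer than four women enroll at a site within 28 calendar days, delivery becomes individual.

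**Endpoint.** Sections 1.1, 2.3 and 13 call the STI outcome cumulative incidence. Section 2.3 powers it thus: "we assumed a 50% reduction (on a background cumulative incidence of 20.5%) to be clinically meaningful to detect via Poisson regression", and reports that "80% power is achieved for the rate-limiting outcome (i.e., cumulative STI incidence) with an effective sample size of 372 participants". The Data Analyses Plan says: "To test the difference in the new incidence of any STI (primary outcome) at the 12-month follow up, logistic regression models will be used".

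**Swabs.** Section 3.5 (Biological Assays) describes a swab after the baseline assessment. The payment list in section 3.7 shows interviews only at 3 and 6 months, then a payment "for completing the 12-month follow-up interview and STI test and HIV test". It also lists a bio retesting payment with no timing or purpose.

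**The concern.** The trial compares the proportion of women with a new STI between two swabs, so the interval between those swabs should not depend on the arm. Here it does. The baseline swab precedes randomization for everyone, but the 12-month clock starts at once for control and only after group formation and four sessions for E-WORTH. The extra time at risk falls on the experimental arm alone and works against it. Women who drop out of E-WORTH have no rule for dating their visits, yet an intention-to-treat analysis must include them.

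The endpoint's name adds to this. A cumulative endpoint is sensitive to length of follow-up, and same-day positivity much less so. The documents use the first name while the described testing points to the second. The plan says *new* infection but gives no rule for women positive at baseline. Section 3.7 foresees hard-to-reach women who "tested positive for an STI and need to be treated as soon as possible before they are due for 12 month follow up".

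**Working it through.** **Inputs.** From section 2.3: control 20.5%, halved to 10.25%; effective N = 372 (186 per arm), 378 after ICC, 420 after 10% attrition. From section 13: alpha .05, two-sided. From section 3.5 (Randomization): 1:1 allocation.

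**1. The plan's own figure.** A standard null-variance (Signorini) formula for Poisson regression with a balanced binary covariate is

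N = [z(.975)·√V0 + z(.80)·√V1]² / (λ0·β²)

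with V0 = 1/(0.5 × 0.5) = 4, V1 = 1/0.5 + 1/(0.5 × 0.5) = 6 and β = ln 0.5, so β² = 0.4805.

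- Numerator: (1.960 × 2 + 0.842 × 2.449)² ≈ 35.8.
- λ0 = 0.205: N ≈ 363, or 80.8% power at 372.
- λ0 = 0.20: N ≈ 372.
- Later steps: 378/372 = 1.016 and 378/0.9 = 420.

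The stated 80% at 372 therefore reproduces.

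**2. Power for the analysis actually planned.** For a binary outcome I used the pooled two-proportion (score) approximation at 186 per arm. The mean proportion is 0.15375, the null standard error 0.0374 and the alternative standard error 0.0370.

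z = (0.1025 − 1.960 × 0.0374)/0.0370 ≈ 0.79, so power = 78.5%.

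The same calculation gives 79.1% at 378 and 83.2% at 420. A likelihood-ratio test by exact enumeration gives 79.4%, 80.1% and 84.1%.

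**3. The clock, arm by arm.**

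| | Control | E-WORTH |
|---|---|---|
| Baseline swab | before randomization | before randomization |
| Testing session | immediately | immediately |
| Further sessions | none | four |
| Wait for a group | none stated | up to 28 days |
| Start of 12-month clock | at once | after the last session |
| Non-completer's clock | single session, so rarely an issue | not defined |

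The difference follows from the plan's own rules, but its length does not, because no interval between sessions is given.

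**4. Size, as an illustration.** *Assumptions:* roughly weekly sessions (about 4 weeks) plus a 0 to 28 day wait, hence 1 to 2 extra months; constant hazard; infections accumulating over follow-up.

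- 13 months: 1 − (1 − 0.1025)^(13/12) = 0.111; 0.111/0.205 = 0.54.
- 14 months: 1 − (1 − 0.1025)^(14/12) = 0.119; 0.119/0.205 = 0.58.

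Putting these into the step 2 formula at 186 per arm:

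| E-WORTH interval | Apparent risk ratio | Power |
|---|---|---|
| 12 months | 0.50 | 78.5% |
| 13 months | 0.54 | 71% |
| 14 months | 0.58 | 62% |

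**5. The endpoint.** The assay section gives a baseline swab, the payment list attaches an STI test to month 12 only, and the Data Analyses Plan tests new STI at month 12. Together they point to one scheduled post-baseline swab. This is an inference: no section sets out a follow-up swab schedule, and the retesting payment is unexplained. A single swab cannot detect infections acquired and cleared or treated between visits, so it does not observe cumulative incidence as usually understood.

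**The case against.** **On power.** A reader might infer that the change from Poisson to logistic regression, or reliance on one swab, means the design fails to deliver 80%. The documents do not support that.

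- The figure reproduces by a standard Poisson formula, and the planned logistic test comes within about 2 points at 372.
- Other Poisson variants give less (a Wald formula gives 69.5%), but that test is not planned for this outcome.
- Power of 52%, 63% or 72% would need control positivity of 12%, 15% or 18%. No section gives such rates.
- The source and testing frequency behind the 20.5% are not stated, so it may already be a single-swab figure.

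**On the clock.** Post-intervention timing is a legitimate choice when the interest is durability after the last exposure. Weekly sessions are assumed, and individual delivery limits the wait for a group. The risk-ratio figures treat the endpoint as accumulating, whereas a single swab may mainly show infection present that day, when extra weeks matter less. All of this limits the size. It does not remove the arm-dependent interval or supply a date for non-completers.

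**On persistent infection.** The analysis plan specifies new incidence and adjusts for baseline attributes of the outcome. The protocol provides single-dose treatment with confirmation, and an incentive to complete treatment before month 12. Nothing says untreated baseline infections count as new. What stands is that no written rule says they do not.

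**Conclusion.** The timing point holds. The plan's own rules make the baseline-to-12-month interval longer for E-WORTH than for control, in the direction against E-WORTH, and leave non-completers undated. The size is uncertain: a risk ratio of 0.54 to 0.58 instead of 0.50, and power of 71% to 62% instead of 78.5%, apply only under the assumed 1 to 2 extra months, constant hazard and accumulation over follow-up. The true effect is smaller to the extent that the swab reflects current infection.

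The labeling point also holds, with the single follow-up swab inferred rather than stated. The stated 80% power is not shown to be wrong. This is an inexpensive improvement to comparability and clarity, not a failure of the sample size.

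**What to change.** 1. In sections 2.1 and 3.2, date the 12-month STI assessment, and the 3- and 6-month visits, from randomization in both arms, with the same windows for completers and non-completers.
2. State the swab schedule, including what the retesting payment covers.
3. In sections 1.1, 2.3 and 13, name the endpoint as new STI (any of the three organisms) on the 12-month swab, matching the Data Analyses Plan. Keep *new*.
4. Add a sensitivity analysis limited to organisms negative at baseline or with confirmed treatment.
5. In section 2.3, give the source and testing frequency of the 20.5%. If the power paragraph is touched, report the logistic figure beside the Poisson one (about 78.5% at 372, 79% at 378).

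**Cost.** Wording in both documents and a visit-window amendment, with no extra participants. The one real downside is that E-WORTH women are assessed somewhat less than 12 months after their last session (about 10 to 11 months under the assumed schedule), so the claim about durability is slightly shorter.
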